#### 2.3.3 Live monitoring tools

The live monitoring of the observed OPDs’ emotional and behavioral reactions is very important because the deficit in the short-term memory of OPDs does not allow to gather reliable data about their emotions and thoughts, even if asked at the end of the intervention session. Thus, the use of further tools for monitoring the effects of the intervention during the delivery of the SOUND activities is included (Table 2).

DCPs and OPDs, who will have provided their written or audio recorded verbal consent, will be video recorded by two cameras (for having two points of view and minimize blind points) during the delivery of the SOUND sessions. The recordings will be watched by the researchers who will analyze and interpret participants’ behaviors with the aim to evaluate the method and improve it.

Collecting information on OPDs and DCPs’ emotions is important to understand if there is an emotional synchronization between the two types of beneficiaries, that may contribute to overcome the professional-patient asymmetry and so increase the chances for a successful intervention. Such observations can be collected from the analysis of the video recordings. Furthermore, the research protocol includes an *ad hoc* instrument for this purpose, the Live Session Emotions Thermometer (LSET)^3^. LSET is an idiosyncratic tool for monitoring the emotions of both DCPs and OPDs during the activities which includes two forms, one for recording the OPDs observed emotional reaction and one for noting the professionals’ own reaction and how they handled the situation. This form encompasses quantitative and qualitative data. The tool includes the image of a thermometer with 10 degrees, where 1 indicates the lowest and 10 the highest intensity of the emotion. In the first form, the observer (DCP) identifies and writes down the prevalent emotion of the observed person (OPD) e.g., happiness or sadness, scores its intensity by crossing the corresponding degree in the thermometer, and describes the observed behavioral reaction and the activity that took place in that moment. In the second form, DCPs will report their own emotion, scored by intensity, their thoughts, their behavioral reaction (strategy adopted to handle the situation) and their sense of efficacy regarding the occurred episode. DCPs are requested to fill the LSET immediately after every SOUND session.

In addition, the external observers (i.e., the researchers), will be focused on each OPD and will fill-in the Apparent Affect Rating Scale (AARS; Lawton et al., 1999). The AARS is an observational tool designed for research purposes in the dementia field. The scale aims to rate five emotions, two of which positive (pleasure and interest) and three negative (fear/anxiety, anger and sadness), and their duration on a scale from 0 to 5 (0 = can’t tell; 1 = never; 2 = less than 16 secs; 3 = 16–59 secs; 4 = 1–2 mins; 5 = more than 2 mins) by observing the person for 5 min.

#### 2.4 Data analysis

The analysis plan includes, for quantitative data, outcomes description. Normality in distribution of continuous variables will be assessed via Shapiro-Wilk test and the following measures will be reported: mean and standard deviation for normally distributed variables or median and interquartile range for non-normally distributed variables. Absolute frequency and percentage will be reported for categorical variables. Comparisons between outcomes and exposures will be made using the Chi Square test, (in the case of categorical variables) or *t*-test or F-Anova (in the case of comparisons between normally distributed continuous variables and the groups), or by non-parametric tests such as Wilcoxon rank-sum test or Kruskal-Wallis test (in the case of comparisons between non-normally distributed continuous variables and the groups). Through Pearson’s or Spearman’s correlation we are going to study the relationship between continuous variables as appropriate according to variables’ distribution. Temporal comparisons (T0 vs. T1, T0 vs. T2, or T1 vs. T2) will be conducted by *T*-test for paired samples. Possible multivariate models will be assumed in case of significant differences in outcomes at the univariate level: coefficients and standard errors or odds ratios and 95% confidence intervals will be reported according to the typology of outcomes (continuous or binary). Goodness of fit will be determined by R-squared of pseudo R-squared as appropriate. Subjects withdrawing from the study will not be replaced, according to the intention to treat (ITT) principle. Sequential imputation using chained equations method will be applied in case of missing values in covariates. Statistical analyses will be conducted by a statistician, who will be blind to group allocation prior to analysis. The significance threshold will always be set at p < 0.05. The software used for the analyses will be SPSS for Win V24.0 (SPSS Inc., Chicago, IL, USA).

Qualitative data from the open-ended questions, included in the *ad hoc* questionnaire for professionals, in the LEWT and in the LEST, will be analyzed thematically (Braun and Clarke, 2006). The textual data will be analyzed by two independent researchers and checked by a third one (add reference). The notes taken by researchers during the watching of the SOUND sessions’ video recordings will be reported into a narrative (Kutsche, 1998) and all narratives will be summarized cross-nationally. Then the narratives will be coded to select and emphasize relevant information answering the research questions and the codes will be merged in themes (De Munck and Sobo, 1998). The textual data will be analyzed by two independent researchers and checked by a third one for minimizing the bias of subjectivity (Golafshani, 2003).

The datasets that will be generated and/or analyzed during the pilot study will be available from the corresponding author on reasonable request.

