### 2.2 Conditions

#### 2.2.1 Participants

In every study country, 15 OPDs and 15 DCPs will be recruited and participate to the experimentation, for a total of 45 OPDs and 45 DCPs (90 people overall). OPDs and DCPs’ inclusion and exclusion criteria are summarized below (Table 1).

**TABLE 1 T1:** Participants’ selection criteria.

Type of participants	Inclusion criteria	Exclusion criteria
OPDs	• Interest in the project and signed consent form • Age 65 + • To be able to see, hear and move • Diagnosis of MCI or dementia with mild to moderate impairment (MoCA total score ≥ 10/30) • Absence of aphasia (mild acceptable) • Be able to understand and undertake simple task as required during activities	•Lack of consent to participate • Age 65− • Not be able to see, hear and move even with the help of appropriate aids • Absence of formal diagnosis of MCI or dementia or severe level of impairment (MoCA total score ≤ 10/30) • Moderate to severe aphasia • Not able to understand and undertake simple task as required during activities
DCPs	• Having experience in the dementia field (e.g., educators, occupational therapists, physiotherapists, psychologist, sociologists, nurses, music therapists, professional caregivers, doctors) • Having interest in the project and signed consent form • For the (co-)facilitators and internal/external observers: having completed the SOUND training	• Lack of experience working in the dementia field • Lack of consent to participate • For the (co-)facilitators and internal/external observers: lack of completion of the SOUND training

Older people with dementias will be recruited from the study organizations, health care dementia services and community services such as diagnostic centers, dementia day care centers, residential care facilities and charities. Individuals will already have a formal diagnosis of MCI or dementia. Their level of cognitive impairment is routinely assessed by the health professionals of the organization to which they belong. Therefore, these health professionals will support the recruitment and selection processes. Ethical approval has been obtained depending on the national legal requirements. OPDs retention will be empowered by collaborating with their professional caregivers who will present the SOUND activities as a pleasant novelty and as a gift.

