#### 2.2.2 The SOUND intervention

The intervention will be implemented in Italy, in an Alzheimer day-care center, and in Portugal and Romania, in older people care facilities hosting people with dementia, where the DCPs who will be involved would regularly work. It includes 12 sessions delivered twice a week, for a 6-week period. Although there is no consensus regarding the frequency required for music-based interventions (Moreno-Morales et al., 2020), past research suggests that a higher occurrence may be more impactful (Carr et al., 2013).

During the intervention, OPDs and DCPs are positioned in a circle and everyone plays a specific role within the circle. OPDs will be the participants to whom the intervention is delivered. DCPs will implement the intervention by undertaking specific roles, i.e., the roles of facilitator, co-facilitator or internal observer. The role of facilitator will be assigned to a musician or a DCP with music skills, previously trained in the SOUND method. During the sessions, the facilitator proposes the activities to the participants in a responsorial style, holds the circle, welcomes and repeats any spontaneous and unexpected activity coming from the participants and proposes it to the whole circle. A DCP will be the co-facilitator, who is responsible for supporting the facilitator during the session. The role of internal observers, generally four per SOUND session, will be assigned to the rest of recruited DCPs: their task is to support the OPDs during the intervention in a non-intrusive and facilitating way while taking part in the activity. Facilitator, co-facilitator and internal observers take mental notes of their observations for reporting them in writing at the end of each session by using the live monitoring tools reported in Table 2. Four researchers (for covering all the sections of the circle circumference) will be the external observers: they will focus on OPDs’ emotional and behavioral responses to the proposed activities and take notes through dedicated tools (Table 2).

**TABLE 2 T2:** Live monitoring outcomes tools.

Target group	Tools	Variable	Point of view	When it is used
Dementia care professionals	Video recording	Behavior	Video camera (researcher)	During SOUND sessions
	Live Session Emotions Thermometer	Emotional state, behavioral reaction	Self-report	After each SOUND session
Older people with dementia	Video recording	Behavior	Video camera	During SOUND sessions

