All study-related information will be stored securely at the study site. All participant information will be stored in locked file cabinets in areas with limited access. All reports, data collection, process, and administrative forms will be identified by a coded ID [identification] number only to maintain participant confidentiality. All records that contain names or other personal identifiers, such as informed consent forms, will be stored separately from study records identified by code number. All local databases will be secured with password-protected access systems. Forms, lists, logbooks, appointment books, and any other listings that link participant ID numbers to other identifying information will be stored in a separate, locked file in an area with limited access.

The scientific integrity of the study requires that the data from all SOUND sites (i.e., Italy, Portugal and Romania) be analyzed study-wide and reported as such. All results coming from the data collected through this protocol are expected to protect the integrity of the major objective of the study at the time of their dissemination through scientific papers and oral presentations, that will be agreed in the Steering Committee (made of the Authors).

The primary outcome papers of SOUND i.e., those reporting the effects of the intervention on OPDs’ wellbeing and DCPs’ burnout will be presented by the first author to the Steering Committee for approval as well as secondary outcome papers and presentations (e.g., on DCPs’ cooperation or OPDs’ reduction of neuropsychiatric symptoms). The study results will be released to the participating DCPs, OPDs, informal caregivers and the general medical community.

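### Correlations pooled over three countries without a country term may partly reflect country differences in level; adjust those between score levels for country

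*Protocol article*

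**What the plan says.** The relevant statements are all in the protocol article.

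- **Section 2.4 (Data analysis).** By Pearson's or Spearman's "correlation we are going to study the relationship between continuous variables as appropriate". The choice between the two rests on distribution alone. The section does not say which variables are correlated, or whether levels or changes are used. On significance: "The significance threshold will always be set at p < 0.05". Multivariable models are only a possible further step after significant univariate differences, and no covariates are listed for them. Country is not named in the section.
- **Section 2.5 (Ethics).** Integrity, the article holds, "requires that the data from all SOUND sites (i.e., Italy, Portugal and Romania) be analyzed study-wide and reported as such". The sentence stands among rules on reporting and publication.
- **Section 2.2.1 (Participants).** "In every study country, 15 OPDs and 15 DCPs will be recruited and participate to the experimentation".
- **Section 2.2.2 (The SOUND intervention).** Delivery is "in Italy, in an Alzheimer day-care center, and in Portugal and Romania, in older people care facilities hosting people with dementia".
- **Section 2.3.2 and Table 3.** Section 2.3.2 makes the NPI informant a family or a professional caregiver according to where the person lives, and allows either for the patient version of the LEWT. Table 3 lists only the family caregiver for both. WHO-5, MoCA, FAB and HADS are answered by the older person in every country.

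**The concern.** A correlation over pooled groups mixes two things: how the variables move together within a country, and how the country averages line up. If both variables are higher in the same countries, the pooled coefficient is positive even when they are unrelated within every country. This is a bias in the estimate itself, distinct from any question about standard errors.

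Differences in level between the sites are plausible. The setting is day care in Italy and care facilities in Portugal and Romania. For the NPI and the patient LEWT the type of informant may follow the setting, which could move both scores together.

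What is at stake is interpretation. A pooled correlation between, say, NPI and LEWT levels could be read as a link between symptoms and emotional state when part or all of it is a difference between sites.

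**Working it through.** **Inputs.** From the protocol: 15 per country in three countries, 3 × 15 = 45, which matches the stated total of 45 older people (and likewise 45 professionals); significance threshold 0.05. The protocol has no power figure or target correlation to reproduce. Assumed: two-sided testing, within-country SD of 1, zero within-country correlation, and the size and pattern of the country shifts.

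**Formula.** With equal country sizes and no within-country correlation, the pooled correlation is approximately

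r = c / √[(1 + v₁)(1 + v₂)],

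where v₁ and v₂ are the variances of the country means of the two variables and c is their covariance. If both variables have the same country means, c = v₁ = v₂ = v and r = v / (1 + v). If only one variable shifts, or the two patterns are uncorrelated, c = 0 and r = 0.

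- Italy versus the other two (means 0, d, d): v = (2/9)d². At d = 1, r = 0.222/1.222 = 0.18.
- Steps (means 0, d, 2d): v = (2/3)d². At d = 0.5, r = 0.167/1.167 = 0.14. At d = 1, r = 0.667/1.667 = 0.40.

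**Simulation.** There were 20,000 data sets per scenario. The pooled Pearson test (43 df) was compared with the test on country-centred values (41 df).

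| Country pattern (SD) | Mean pooled r | False positives, pooled | False positives, country-adjusted |
|---|---|---|---|
| No shift | 0.00 | 5.0% | 5.0% |
| Italy v rest, 0.25 | 0.01 | 5.0% | 5.0% |
| Italy v rest, 0.5 | 0.05 | 6.1% | 5.1% |
| Italy v rest, 0.8 | 0.13 | 12.7% | 5.3% |
| Italy v rest, 1.0 | 0.18 | 22.4% | 5.0% |
| Italy v rest, 1.5 | 0.34 | 65.4% | 5.0% |
| Steps of 0.25 | 0.04 | 6.1% | 5.1% |
| Steps of 0.5 | 0.14 | 15.4% | 5.1% |
| Steps of 0.8 | 0.31 | 55.1% | 5.2% |
| Steps of 1.0 | 0.41 | 83.4% | 5.2% |
| One variable only, 1.0 | 0.00 | 5.2% | 5.0% |
| Both shift, patterns uncorrelated | 0.00 | 3.5% to 4.8% | 4.9% to 5.2% |

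Steps of 1.0 put 2 SD between the outer countries. Pooled Spearman behaves like pooled Pearson (21.6% for Italy v rest at 1.0), so choosing the rank method gives no protection. The adjusted column was run for the Pearson version only.

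**Cost of adjusting.** Critical |r| = t / √(df + t²). This gives 0.294 at 43 df and 0.301 at 41 df. Separate correlations in each country (n = 15, 13 df) would need |r| above 0.514.

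**The case against.** The strongest reply is that this is silence in a condensed article. The correlation takes one sentence, adjustment may be set out in a fuller plan, and nothing in 2.4 bars country as a covariate. The study-wide requirement stands among publication rules, and a country-adjusted analysis is study-wide too. All of that is fair, and applying the requirement to the correlations is an inference. What remains is that the article does name a method, simple bivariate correlation, and does say that the sites' data are analysed together. Carried out literally, that yields the pooled coefficient examined here.

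A reader might go further and infer that country differences will produce false relationships in this trial. The documents do not support that. They give no between-country figures, and the artefact needs both variables to shift in an aligned pattern. For the one setting contrast that is documented, Italy against the other two, the error rate barely moves up to 0.5 SD.

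A reader might also infer that differing informants or translations affect all the scales. The informant question reaches only the NPI and the patient LEWT, depends on residence rather than country as such, and is described differently in Table 3 and section 2.3.2. WHO-5 and BAT are self-answered. No effect of language on level is documented: section 2.3.2 calls the NPI well established across translations and cites validation of the BAT in all three countries.

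Nor do the documents support a warning about response to SOUND in general. Stable level differences cancel in changes from T0.

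**Conclusion.** The point holds in limited form. The plan as worded allows correlations of score levels to mix between-country with within-country association, and a specific method that avoids this is available at almost no cost. The size cannot be fixed from the documents. Under the assumptions above it runs from nothing (about 5%) to large (22% for a 1 SD contrast of Italy with the rest, 83% for aligned steps of 1 SD), and the upper figure is the far end of an assumed range.

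The consequence is confined to exploratory correlations of levels. The paired T0, T1 and T2 comparisons, which carry the primary outcomes, are not touched, because each person is compared with themselves. None of the results that the Discussion says it expects is a correlation.

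**What to change.** Add one sentence to section 2.4: correlations between score levels pooled over countries will be partial Pearson or Spearman correlations adjusted for country, or equivalently will be computed on country-centred values or within-country ranks. State in the same place whether each planned correlation uses levels or changes.

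This remains a study-wide analysis in the sense of section 2.5, since it pools the within-country information from all three sites. It needs no new data and costs two degrees of freedom. If the countries turn out not to differ, almost nothing is lost.

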Non-pharmacological treatments, including music-based intervention, can have a positive effect also on healthcare workers (Cabrera et al., 2015). A qualitative study on music and dance interventions in dementia care found that healthcare staff had increased positive interactions, relationships, communication, sense of confidence, empathy, and an improved understanding of residents’ emotional state and experience of limitations (Melhuish et al., 2016). Such aspects, together with the team cohesion, work engagement and job satisfaction, contribute to preventing stress and burnout of healthcare staff (Maslach and Leiter, 1999; Öhman et al., 2017; Costello et al., 2018). However, there are few music-based treatments targeted to care professionals and none, to the best of our knowledge, involving both dementia care professionals and older patients.

Thus, even if the practice and part of the scientific literature, confirm the power of music in improving OPDs’ functions and care professionals’ well-being at the work place, the quality of evidence is low and so further research is needed (Dyer et al., 2017).

Considering the above, further studies should include emotional well-being and social outcomes to improve the knowledge about the effects of music on older people with dementia and dementia care professionals to support the implementation of music interventions as a care strategy.

This protocol has been designed to cover this knowledge gap by testing an intervention based on active and passive music activities delivered in circle with older people with mild cognitive impairment and mild to moderate dementia, and dementia care professionals. Particularly, the study aims to investigate two principal factors: 1) the efficacy of the SOUND intervention on OPDs; and 2) the impact of implementing the SOUND intervention on the DCPs who are delivering it as a novel group. Overall, the pilot study aims to assess the feasibility and preliminary outcomes of the protocol. The study is part of the SOUND project, funded by the Erasmus + program (contract 2021-1-IT02-KA220-ADU-000033494) and aimed at designing an original music-based curriculum for dementia care professionals and testing a pilot music-based intervention with OPDs in Italy, Portugal and Romania. At the time of writing this manuscript, we were about ending the training for dementia care professionals and planning the intervention that will be concluded in the three countries in early 2024.

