DCPs will be selected among those who have successfully completed the SOUND training i.e., a 22-h training based on an original SOUND curriculum^1^ co-designed with OPDs, DCPs and family caregivers in Summer 2022. The training was implemented in Spring 2023 in the three study countries, by means of an e-learning platform, called Virtual Music Circle (VMC), specifically developed within the SOUND project, and of face-to face lessons, to train the professionals who will be involved in the intervention. The SOUND training concept and learning outcomes are deepened in a dedicated paper (Quattrini et al., under review)^2^. The training was open to entire teams of participating organizations. Selected DCPs will include permanent staff and trainees who may or may not have an established relationship with OPDs. DCPs will be required to study OPDs biographies to properly relate to OPDs during the intervention considering their needs and characteristics. None of the selected DCPs used the SOUND intervention prior to the trial, therefore all of them will apply it for the first time. The total number of people per every SOUND activities group will be of about 15, including both OPDs and DCPs. For example, one group may include eight OPDs, five DCPs, the facilitator and the co-facilitator. The other group may be made of seven OPDs, four DCPs, the facilitator and the co-facilitator. This will be made to guarantee the correct delivery of the intervention and provide the conditions to enhance its potentials. In fact, small-sized units of 5–15 people can positively impact older people’s well-being, behavior, functioning, and activity engagement (Verbeek et al., 2009) and doing activities in small groups can hinder the participants’ cognitive decline (Kok et al., 2016) and favor social connection (Van Zadelhoff et al., 2011) more than in large groups.

An attendance sheet will be used to monitor participation, whereby absence from half or more of the sessions will result in a drop-out.

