The activities and music are carefully chosen in order to elicit in participants only feelings of peace and well-being, as previous similar experiments have shown (Caldini et al., 2019). In compliance with the Declaration of Helsinki (stating that “the protocol should describe arrangements for post-study access by study participants to interventions identified as beneficial in the study or access to other appropriate care or benefits”), should this study provide evidence of the effectiveness of SOUND, the SOUND activities will be included in the routine of the dementia care centers. This goal is probable and achievable because a total of 63 professionals have been trained on the SOUND method, 29 in Italy, 17 in Portugal and 17 in Romania; moreover, the Virtual Music Circle training platform is predisposed to train further professionals (Quattrini et al., under review, see text footnote 2).

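### The plan claims a statistician blind to group allocation, but every participant is in the SOUND arm: the safeguard does not exist, and pre-post change alone cannot show efficacy

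*Protocol article*

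**What the plan says.** On recruitment, Section 2.2.1 states: "15 OPDs and 15 DCPs will be recruited and participate to the experimentation, for a total of 45 OPDs and 45 DCPs". It then gives an example of how a country's participants are divided into circles: "one group may include eight OPDs, five DCPs, the facilitator and the co-facilitator" and "The other group may be made of seven OPDs, four DCPs, the facilitator and the co-facilitator". Section 2.2.2 describes OPDs as those who receive the intervention and dementia care professionals (DCPs) as those who deliver it, as facilitator, co-facilitator or internal observer. No section describes a control, waiting-list or usual-care group, or any step that assigns people to one.

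On analysis, Section 2.1 describes pre-post and longitudinal comparisons. Section 2.4 opens its list of tests differently: "Comparisons between outcomes and exposures will be made using the Chi Square test". It continues with t-test or ANOVA, and rank-sum or Kruskal-Wallis, across groups that it does not define. Comparisons between T0, T1 and T2 are given a separate sentence and one method, the paired t-test. The section also says of the statistician: "Statistical analyses will be conducted by a statistician, who will be blind to group allocation prior to analysis".

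On purpose, the Introduction names as the first aim "the efficacy of the SOUND intervention on OPDs". The title also speaks of efficacy and the Abstract of effectiveness. Section 2.5 adds: "should this study provide evidence of the effectiveness of SOUND, the SOUND activities will be included in the routine of the dementia care centers". The Abstract and Introduction also call the study a pilot of feasibility and preliminary effects.

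**The concern.** Blinding the statistician to allocation protects the comparison between arms. With one arm there is nothing to conceal, so the sentence credits the study with a protection against bias that its design cannot provide. A reader who meets that sentence next to a list of between-group tests could take the study for a controlled comparison.

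What is at stake is how the result is read. The two primary outcomes, WHO-5 for OPDs and the Burnout Assessment Tool for DCPs, can inform on SOUND only through change from T0. Such change combines any effect of SOUND with the passage of time, extra attention, expectation, repeat testing and regression to the mean. The limitations in the Discussion cover national sample size, clinical parameters, family caregivers, the OPD-DCP relationship and observer subjectivity. They do not mention the missing comparator.

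**Working it through.** **1. Is anyone left to be allocated elsewhere?** Inputs from Section 2.2.1: circles of 8 and 7 OPDs per country, three countries, 45 OPDs in total.

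- OPDs in SOUND circles per country: 8 + 7 = 15.
- Over three countries: 15 × 3 = 45, which reproduces the stated total.
- OPDs remaining for a comparison group: 45 − 45 = 0.
- DCPs seated in the example: 5 + 2 + 4 + 2 = 13 of 15. The example is only illustrative. Section 2.2.2 gives the observer role to the rest of the recruited DCPs and holds none back as a comparison group.

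The 45 is a head count. Section 2.1 bases the sample on sampling for meaning, so there is no power calculation to reproduce.

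**2. Which planned test bears on SOUND?**

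| Test in Section 2.4 | What it can compare here | Informs on SOUND? |
|---|---|---|
| Chi-square, t-test/ANOVA, rank-sum, Kruskal-Wallis | Subgroups: country, diagnosis, sex, living condition, DCP role | No: every subgroup is in SOUND |
| Paired t-test | T0, T1 and T2 within person | Yes, but without control |

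The section checks normality and offers a non-parametric alternative for the subgroup tests. The paired comparison has no such alternative. Section 2.4 foresees binary outcomes (odds ratios), and the Discussion expects absence of depression and anxiety on the HADS, but no paired test for a binary change is named.

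**3. How often would the paired test be significant if SOUND had no effect?** Let WHO-5 (percentage score) shift by s points for other reasons. The article gives no SD of change, so I assume 15, 20 and 25. I also assume a two-sided test at 0.05 (sidedness is not stated), n = 45 with no dropout, and independent participants.

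Noncentrality: λ = s × √45 / SD, with √45 = 6.708. The rejection probability comes from the noncentral t distribution with 44 degrees of freedom.

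| Shift s | SD 15 | SD 20 | SD 25 |
|---|---|---|---|
| 3 points | λ = 1.34, 0.26 | λ = 1.01, 0.17 | λ = 0.80, 0.12 |
| 5 points | λ = 2.24, 0.59 | λ = 1.68, 0.38 | λ = 1.34, 0.26 |

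The nominal level is 0.05. The real size of s cannot be learned from this design.

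**4. Is there any internal check on a prior trend?** T0 is one week before the intervention, the intervention lasts 6 weeks, and T2 is 2 weeks after it. That gives (1 + 6 + 2) × 7 = 63 days, which matches the 63 daily thermometer (LEWT) ratings in Section 2.3.2. Seven of those days precede the intervention.

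**The case against.** The best defence is that this is openly a pilot. The Abstract and Introduction speak of feasibility and preliminary effects, Section 2.1 explains why a randomised trial was not chosen, and the pre-post comparison is described plainly. The sentence in Section 2.5 is conditional and belongs to a post-study access clause. No estimate, p-value or sample size depends on the blinding sentence. All of this stands, and it limits the point to what is claimed and concluded. It does not give the blinding sentence a meaning. The softer wording also sits beside the efficacy aim without replacing it.

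Two escapes can be considered. The circles are also called groups, so allocation might mean allocation to a circle; but both circles receive SOUND, and masking circle would not protect the pre-post comparison. Figure 1 is not shown, but the text leaves no OPDs for a second arm.

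A reader might infer more than the article supports:

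- **That independent-sample tests are to be applied to repeated measurements, giving wrong p-values.** Section 2.4 assigns those tests to exposures and groups, and the paired t-test to the time points.
- **That country is the only available grouping.** Diagnosis, sex, living condition and DCP role are also recorded or defined, and exploratory comparisons across them are legitimate.
- **That the paired t-test is invalid for any skewed score.** It depends on the distribution of the within-person differences, and with about 45 pairs it is usually a reasonable approximation.

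Naming fallback tests could ordinarily be left to a fuller document. It is raised here only because the article sets out a fallback for the subgroup tests and then fixes the paired comparison to one method.

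**Conclusion.** The blinding sentence is wrong as written: all 45 OPDs are in SOUND circles and the article describes no allocation. That conclusion rests on the text and the head count and needs no assumption about variability. It follows that the between-group tests do not estimate an effect of SOUND, and that the paired comparison, which alone bears on it, supports a statement about uncontrolled change and not about efficacy or effectiveness.

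The probabilities of 0.12 to 0.59 only illustrate the risk. They rest on assumed shifts of 3 or 5 points and assumed SDs of 15 to 25. The bias itself cannot be bounded from this design. The error concerns what the study may claim and can be cured by rewording and a few named tests. The paired analysis of T0, T1 and T2 remains usable.

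**What to change.** 1. **Blinding.** Delete the allocation-blinding sentence from Section 2.4. Alternatively, replace it with masking of the T0/T1/T2 labels until the analysis code is final, where the data allow. The post-intervention DCP questionnaire has extra questions about the intervention (Section 2.3.2) and would reveal its time point, so masking cannot cover it.
2. **Groups.** Define the exposures and groups, and label the independent-sample tests as exploratory subgroup comparisons.
3. **Paired tests.** Extend the existing normality check and non-parametric fallback to the temporal comparisons: signed-rank for non-normal differences, and McNemar for any binary change, such as absence of depression or anxiety on the HADS.
4. **Conclusion.** In the title, Abstract, Introduction and Section 2.5, replace efficacy and effectiveness with preliminary, uncontrolled change from T0.
5. **Limitation.** List the missing comparator in the Discussion.
6. **Prior trend.** Report the 7 pre-intervention LEWT days as a limited check. They cover emotional wellbeing only and cannot stand in for a control group.

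The cost is wording, a few named tests and a weaker claim, which is the one the design supports. No new participants or staff are needed. Splitting the present sample would not be a substitute. For a 10-point WHO-5 difference and assumed SDs of 15, 20 and 25, two arms drawn from 45 OPDs give about 61%, 39% and 27% power, while 80% power needs 36, 63 and 99 OPDs per arm.
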